### Statistical analysis

Analysis is to be performed using the R statistics package (version 3.1.1). All data will be inspected visually and statistically for normality (skewness and kurtosis between -1 and +1). Analysis of variance (ANOVA) and chi-squared tests of independence will be used to check for any differences between groups at study entry, any differences found here will be controlled for in that outcome analysis. Outcome analysis will take the form of ANCOVAs to detect changes between the experimental and control groups at post- treatment while controlling for baseline values and other possible confounders such as age, gender, time since cardiac incident, time since phase-2 CR completion and current exercise regimen or phase-3 CR participation. Multiple imputations will be used to impute missing data for participants with less than 10% missing data. An intention to treat analysis in which all missing data will be managed with multiple imputations will be conducted along with a separate per protocol analysis in which those with greater than 10% missing data or less than 60% yoga session attendance will be excluded. A p-value of less than 0.05 will be considered statistically significant.

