### Sample size and power calculation

To our knowledge, there is at present only one study which examines the effect of yoga training in post-CR patients [52]. This study assessed the effects of a 6 week yoga program on lipid profiles and brachial artery vasodilation in 10 post-CR patients and 23 healthy individuals however published data was insufficient to conduct a preliminary power analysis [52]. Given the DASS is a primary outcome measure in this study, a power analysis was conducted upon the results published in a meta-analysis on yogic effects in depression [34]. Results published by Cramer et al. [34] noted a standardised mean difference of 0.69 compared to usual care across five studies. Application of these findings as a basis for an approximated power calculation resulted in an estimated required sample size of 112 participants. Allowing a 20% drop-out rate, a total of 134 patients will be recruited in the current study. This power calculation has been conducted based on a population other than post-cardiac rehabilitation due to a lack of available data in this patient cohort to permit a more robust calculation. As such, an interim sample size analysis will also be conducted at n = 50 allowing for an acceptable estimate of the population standard deviation and hence considerably more robust sample size calculation to ensure adequate power.

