#### Participant diary

Participants will also be asked to complete a weekly diary documenting drastic changes in diet, commencement or cessation of negative behaviours such as alcohol consumption and smoking, number of hours spent exercising, changes in medication, significant positive or negative life events, adverse events, and compliance to yoga program. These behaviours will be monitored by open-ended questions to be completed weekly. This data will be presented for a descriptive synthesis only with compliance to yoga sessions and adverse events, coded into a binary yes/no format, to be considered for inclusion in analysis of covariance (ANCOVA) models as covariates.

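### Significance tests of baseline differences add covariates to each outcome's ANCOVA, so chance imbalance helps to set the model; the rule should be deleted in favour of one closed list

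*Protocol article*

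**What the plan says.** The Statistical analysis section of the protocol article sets out two routes by which a covariate can enter an outcome model.

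- **Route 1, by test.** "Analysis of variance (ANOVA) and chi-squared tests of independence will be used to check for any differences between groups at study entry", followed by "any differences found here will be controlled for in that outcome analysis". The tested variables are not listed and no separate threshold is given. The only significance level stated is the general one: "A p-value of less than 0.05 will be considered statistically significant".
- **Route 2, regardless of any test.** The next sentence has the ANCOVAs "controlling for baseline values and other possible confounders such as age, gender, time since cardiac incident, time since phase-2 CR completion", and goes on to name current exercise or phase-3 rehabilitation participation. This list is introduced by open-ended wording.

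The Randomization section confirms allocation by computer-generated permuted blocks. The Participant diary section mentions further variables "to be considered for inclusion in analysis of covariance (ANCOVA) models as covariates". Those are recorded after randomisation, are a separate matter, and are not part of this point.

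**The concern.** In a properly randomised trial every baseline difference between arms is due to chance. A test of that difference asks a question whose answer is already known, and its p-value carries no information on whether the variable predicts the outcome. Prognostic value is the reason to adjust, and the rule does not consult it. A variable unrelated to the outcome enters if it happens to differ. A prognostic variable outside the named list stays out if it happens to look balanced.

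What is at stake is mainly pre-specification. The trial has many outcomes, and because the rule works outcome by outcome, the adjusted effects on DASS, quality of life, vascular and cognitive measures could come from different models. None of these models could be written down before the baseline data are examined. The secondary question is whether power or the error rate suffers.

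**Working it through.** **Inputs from the article.** Significance level 0.05 (Statistical analysis; two-sided assumed, and assumed to apply to the baseline tests as well). Standardised mean difference 0.69: "noted a standardised mean difference of 0.69 compared to usual care across five studies". Evaluable size: "resulted in an estimated required sample size of 112 participants", or 56 per arm if allocation is 1:1, a ratio the article does not state.

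**Assumed inputs.** The number of variables tested and all covariate–outcome correlations; the article gives none.

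**1. The plan's own figure.** The power behind 112 is not stated. With 95% power the normal formula gives 2 × (1.960 + 1.645)² / 0.69² = 54.6, so 55 per arm and 110 in total. The noncentral t version gives 112 exactly. At 80% and 90% power it gives 68 and 92. So 112 is reproduced by an unadjusted two-group comparison at 95% power, and the covariate rule does not bear on it.

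**2. Chance of at least one spurious addition.** For k independent true-null tests this is 1 − 0.95^k:

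| k | Chance |
|---|---|
| 5 | 1 − 0.774 = 23% |
| 10 | 1 − 0.599 = 40% |
| 15 | 1 − 0.463 = 54% |
| 20 | 1 − 0.358 = 64% |

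The Outcomes sections alone imply about 30 baseline measures: DASS 4, SF-36 8 + 2, blood pressure and heart rate 3, heart rate variability 5, pulse wave velocity 1, carotid measures 3, blood tests 5, total 31, before cognitive tasks. Many are correlated, which lowers these chances, and the article does not say which are tested. No single k can be taken from it.

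**3. Effect of the rule on the plan as written.** Simulation: 6,000 trials per cell, 56 per arm, outcome SD 1, baseline correlation 0.5, five named covariates at 0.15 each always in the model, and ten extra variables tested at 0.05. The true difference is 0.5 SD for power (assumed) and 0 for type I error.

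| Correlation of each extra with outcome | Power, named list only | Power, named plus selected | Change | Type I error, named plus selected |
|---|---|---|---|---|
| 0 | 89.1% | 88.1% | −1.0 | 4.5% |
| 0.1 | 88.3% | 88.1% | −0.2 | 4.7% |
| 0.2 | 89.1% | 90.8% | +1.7 | 3.5% |

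The simulation standard error is about √(0.88 × 0.12 / 6000) = 0.4 points for power and √(0.05 × 0.95 / 6000) = 0.3 points for type I error. The last row is an extreme case: it assumes that 0.25 + 5 × 0.0225 + 10 × 0.04 = 76% of the outcome variance is explained.

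A separate run of the same plan gave type I error of 4.9% with extras not prognostic and 3.7% at correlation 0.2. A further setting (54 per arm, difference 0.45, named covariates at 0.2) gave power under the rule against the named list alone of 84.2% vs 85.1%, 85.4% vs 85.3% and 87.8% vs 85.7% for extras at 0, 0.1 and 0.2. There, type I error stayed within 0.2 points of the named list at 0 and 0.1, and was 3.1% at 0.2.

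**4. Why the pattern looks like this.** The tests use allocation and baseline data only, never the outcome, so they cannot steer the treatment p-value downwards. Adding an imbalanced variable that is not prognostic slightly inflates the variance of the treatment effect, hence the small loss. When several prognostic extras exist, the worst imbalances are removed from the estimate while the standard error still reflects the rest, hence the conservatism.

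**The case against.** The strongest case on the other side has four parts.

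- **The tests only add terms.** A reader might infer that all covariates are chosen by significance, or that predictors are dropped when they look balanced. The article does not support this: Route 2 has no test attached, and the baseline value and named variables stay in. This objection stands, and the point is limited to the additional covariates.
- **Power.** A reader might infer a general loss of power against a fixed list. Figures of that kind can be produced: if five covariates enter only when they differ, power is 86.4% against 93.5% with all five fixed at correlation 0.2, and 87.4% against 99.7% at 0.3. That is a different plan from the one written. At correlation 0 the order reverses (85.2% against 84.4%). This objection stands too.
- **Condensed article.** Closing a covariate list is commonly left to the full protocol or analysis plan, so the open-ended wording alone would be no finding. That is fair. The add-if-different rule, however, is stated affirmatively and is not an omitted detail.
- **Narrow reading.** The clause may concern only a baseline difference in that same outcome. If so, it is redundant, because baseline values are already controlled for, and deleting it loses nothing.

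None of these gives a reason to keep the rule.

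**Conclusion.** The concern holds as a fault of specification. Beyond the baseline value and the named confounders, covariates enter each outcome's ANCOVA through tests of chance differences, so the models may differ by outcome and are fixed only once baseline data are in hand. A spurious addition is likely enough to matter for reporting: 23% to 64% for 5 to 20 independent tests, with the number of tests assumed.

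The measurable effect is small. Against the protocol's own named list, the power change is about -1 to +2 points. Type I error is nominal to conservative, about 3.7% to 4.9% and lower in some settings where many extras are strongly prognostic. A reader might infer a raised false-positive risk; nothing in the article or the calculations supports that. All power and error figures rest on assumed correlations, and the sample size of 112 is unaffected. The change is worth making because it is standard and nearly free, not because the trial's result is in danger.

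**What to change.** 1. Delete the ANOVA and chi-squared comparisons at study entry and the rule that follows from them. Report baseline data by arm descriptively, without p-values.
2. Use one pre-specified list for all outcomes: the baseline value of that outcome, age, gender, time since cardiac incident, time since phase-2 completion, and exercise or phase-3 participation, all measured at week 0. Remove the open-ended wording, and settle in advance whether the last item is one variable, the other, or both.
3. Label any further adjustment, including for a striking imbalance, as a sensitivity analysis.

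Adding centre is optional.

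**Cost.** Analysis wording only. The list uses six degrees of freedom, or seven if both exercise regimen and phase-3 participation enter; with 112 evaluable participants that leaves 112 − 2 − 6 = 104 or 103 residual degrees of freedom. The downside is that the primary model will not correct for chance imbalances in variables outside the list; the sensitivity analysis covers those.

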### Intervention

#### Experimental group

Participants randomised to the yoga therapy group will receive two supervised yoga sessions per week for a period of 12 weeks. They will also be provided with a simplified take-home yoga program, which they will be instructed to practice once per week. The yoga sessions will be group-based and led by an experienced yoga instructor from Yoga Synergy Pty Ltd (Sydney, Australia) [46]. These sessions will run twice per week for approximately one hour per session (details of yoga sequence and time requirements outlined in Table 1). The hatha yoga program will be similar to that used by the research team in a previous study [45] and will involve teaching beginner students safely and progressively over 12 weeks incorporating *asanas* (poses and postures), *pranayama* (breathing control) and *savasana* (meditation). At the start of each session, a series of introductory movements designed to warm-up the extremities, large joints and spine (*itkata vinyasa* and *utkata danda nadi vinyasa*) will be conducted before moving into a salute to the moon (*candra namaskar*). This will be followed by standing postures which are linked to one another to warm up the body whilst stretching and strengthening the muscles (*trikonasa*, *parsvakona*, *gadja hasta padottana*, *gadja baddha padottana*, *parsvottonasa*, *eka pada*, *virabhadra*). Following this, a series of floor postures which are also linked together will be conducted and include: forward bends, twists, hip opening, back arches, and back arch releases. As participants become more competent with training, an inversion (shoulderstand) is added to help calm and restore the body and nervous system. This is followed by a series of neck and spine releases to ensure participant safety. Participants then sat on the floor and engaged in breathing exercises (pranayama) and then supine meditation/relaxation (*savasana*). All postures and exercises are comprised of a simple and more challenging variant to allow difficulty to be scalable within the yoga program in relation to participant ability and capacity.

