#### Control group

Participants randomised to the wait list control group will receive no instructions about yoga practice for the 16 week trial period (12 week intervention +4 week follow up). Upon their completion of the trial, wait list participants will be given the opportunity to participate within the yoga program.

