#### Safety and adherence

In addition to data collected from participant diaries, each assessment visit will detail any information pertaining to adverse events and yoga session compliance will be monitored through class attendance. As stated previously, this data will be included for ANCOVA models as covariates.

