## Discussion

Secondary prevention is an integral aspect regarding the comprehensive care of patients with CVD. Although it has been shown that CR is effective in positively modifying cardiac risk factors and reducing subsequent cardiac mortality, these benefits appear to plateau and gradually decrease upon completion of CR [92]. As noted by Gupta et al. [93] benefits achieved during CR programs are potentially sustainable at a one year follow up, however, minimal improvement across outcome measures was noted and significant regression was seen in important variables such as 6-minute walk distance, body mass index, diet scores, and smoking status. This is corroborated by evidence from Willich et al. [94] and Boesch et al. [95] who also reported worsening of lipid control at long-term follow points. According to adherence reports by Bittner et al. [96] and Ljubic et al. [97], approximately 50% of CR graduates do not maintain adherence to regular physical activity 5–6 months post-phase 2 CR and further highlights that this poor adherence may be associated with higher levels of psychosocial distress such as depression, anxiety, and stress. Given that numerous studies emphasis the capacity of yoga in positively modifying cardiovascular risk factors [35, 36, 38–45] in addition to psychosocial attenuation [28–34, 98], its application in post-cardiac rehabilitation may assist in sustaining and further supplementing the beneficial effects of phase 2 CR. As such, this study will aim to determine the effect of yoga practice on psychosocial, cardiovascular and cognitive function in post-phase 2 cardiac rehabilitation patients and is expected to provide insight into the short term impact of yoga on traditional and relatively novel cardiovascular risk factors and prognostic markers. In addition, these findings may also provide evidence supporting the incorporation of yoga into standardised CR programs as a practical adjunct to improve the management of psychosocial symptoms associated with CV events in addition to improving patients’ cognitive and cardiovascular functions.

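### The 60% attendance rule in the per-protocol analysis can remove participants from the yoga arm only, so that contrast loses the protection of randomisation and may favour yoga

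*Protocol article*

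**What the plan says.** The Statistical analysis section plans two analyses: "An intention to treat analysis in which all missing data will be managed with multiple imputations will be conducted along with a separate per protocol" comparison. In the second, "those with greater than 10% missing data or less than 60% yoga session attendance will be excluded". The model for both is an analysis of covariance: "Outcome analysis will take the form of ANCOVAs to detect changes between the experimental and control groups at post- treatment while controlling for baseline values", with further adjustment for possible confounders such as age, gender and current exercise. One significance rule follows, with no distinction between the two analyses: "A p-value of less than 0.05 will be considered statistically significant".

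The arms differ in whether the attendance criterion can apply. The yoga arm "will receive two supervised yoga sessions per week for a period of 12 weeks" (Experimental group), and "yoga session compliance will be monitored through class attendance" (Safety and adherence). The control arm "will receive no instructions about yoga practice for the 16 week trial period" (Control group).

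The Discussion remarks, about physical activity after cardiac rehabilitation, that "this poor adherence may be associated with higher levels of psychosocial distress such as depression, anxiety, and stress". Those three states are the constructs of the primary outcome.

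**The concern.** A per-protocol set defined by attendance keeps yoga participants who came often enough and has no matching filter for controls. The controls who would have attended poorly, had they been assigned yoga, stay in. Any prognostic difference between good and poor attenders then enters the treatment contrast.

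The article itself gives a reason to expect such a difference. Its Background says that patients with high anxiety or depression comply less with medication and are less active, and its Discussion links poor adherence to distress. If poor attenders would have had worse week-12 DASS scores whatever yoga did, removing them makes the yoga arm look better.

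What is at stake is the claim of benefit. If the intention-to-treat result missed 0.05 and the per-protocol result passed it, nothing in the section says which one stands.

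**Working it through.** **The threshold.** Two sessions a week for 12 weeks is 2 × 12 = 24 supervised sessions. 60% of 24 is 14.4, so a yoga participant needs at least 15 to stay in. A control has no session count to compare with 14.4.

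**Inputs for the size of the bias**
- From the article: 134 recruited with 20% drop-out, so 134 × 0.8 = 107.2, or about 54 per arm. Equal allocation is assumed.
- Assumed, because the article gives no value: baseline-to-week-12 correlation ρ = 0.6; share of the yoga arm excluded for attendance k = 30% or 40%; correlation r = 0.2 to 0.4 between attendance and a better week-12 score; a two-sided test; a true yoga effect of zero.

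**Closed form.** Treat attendance as a standard normal propensity and remove the lowest share k. The mean propensity of those retained is m = φ(z_k)/(1 − k).
- k = 0.30: m = 0.348/0.70 = 0.497
- k = 0.40: m = 0.386/0.60 = 0.644

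*Attendance related to the week-12 score.* The retained group's outcome shifts by −r·m and its baseline by −ρ·r·m. After adjustment for baseline the bias is −r·m + ρ·(ρ·r·m) = −r·m·(1 − ρ²), and 1 − 0.36 = 0.64.

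*Attendance related only to baseline distress.* The baseline shifts by −r·m and the outcome by −ρ·r·m. After adjustment the bias is −ρ·r·m + ρ·r·m = 0.

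*Relation reversed (better-off patients attend less).* The size is the same as in the first case, but the bias is against yoga.

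**Check by simulation** (6,000 null trials per row, 54 per arm, ANCOVA on baseline, attendance related to the week-12 score; negative favours yoga)

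| k | r | Closed form (SD) | Simulated bias (SD) | Two-sided type I error |
|---|---|---|---|---|
| 30% | 0.2 | −0.064 | −0.061 | 6.8% |
| 30% | 0.3 | −0.095 | −0.097 | 8.8% |
| 30% | 0.4 | −0.127 | −0.126 | 11.6% |
| 40% | 0.4 | −0.165 | −0.167 | 15.0% |

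Independent runs of the same design gave error rates from 6.3% in the first row to 16.1% in the last.

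In the same four settings, attendance driven by baseline distress alone gave a bias between 0.000 and +0.004 SD and an error of 4.5% to 5.3%. The reversed relation gave +0.06 to +0.17 SD. An intermediate case, with one stable trait behind both DASS scores and attendance, gave 0.04, 0.06 and 0.07 SD in favour of yoga and errors of 5.7%, 6.3% and 7.2% (k = 30%; r = 0.2, 0.3 and 0.4).

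**Scale.** The sample size section assumes a standardised difference of 0.69. A false benefit of 0.064 to 0.165 SD is 9% to 24% of that (0.064/0.69 and 0.165/0.69).

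**The alternative estimator.** In the same simulated trials, two-stage least squares with randomised arm as instrument for reaching 60% attendance, adjusted for baseline and keeping everyone, had bias within 0.004 SD of zero and error of 4.1% to 5.2%. Its standard deviation was about 0.22 against 0.17 for the per-protocol estimate at k = 30%, and about 0.26 against 0.18 at k = 40%.

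**The case against.** Four points can be made for the plan.

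1. **The mechanism that the article describes works largely through baseline distress, and the ANCOVA adjusts for baseline.** This stands, and it limits the point. If distress at entry is the only thing that drives attendance, there is no bias. What remains is the part of attendance that goes with a change in DASS during the trial, or with a stable trait that one baseline score captures imperfectly. The article's remarks also concern medication, physical activity and contact with cardiologists rather than class attendance, and the Discussion's link is worded as a possibility.

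2. **The intention-to-treat analysis is named first, keeps everyone, and imputes all missing data.** This also stands. The per-protocol result does harm only if it carries the conclusion.

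3. **An attendance criterion that binds one arm is inherent in any per-protocol analysis against a wait list.** True, but that is a reason to label the result supportive and to use an estimator suited to one-sided non-compliance. It is no reason to treat the two results alike.

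4. **A condensed article may leave the ranking of analyses to a fuller document.** It may, and a missing ranking alone would not be a finding. The finding is the exclusion rule, which the article does fix, placed beside a single significance threshold for both analyses.

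A reader might also infer that the rule, taken literally, removes every control for zero attendance. That is not a realistic reading, since a session-attendance criterion plainly concerns those assigned to sessions.

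**Conclusion.** The point holds as a weakness of the per-protocol contrast, not of the trial's main analysis. The attendance rule filters one arm on behaviour after randomisation, and bias towards yoga is plausible. Its size and sign rest on an attendance-outcome relation that the article does not quantify: from nil, through the 0.06 to 0.17 SD and 6% to 16% type I error shown for the assumed settings, to a bias of similar size against yoga.

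Three stronger statements are tempting, and the article does not support them.
- That the per-protocol result is certain to favour yoga, or would show a benefit even if yoga did nothing: this needs a relation beyond baseline that is assumed, not documented.
- That it sets the most committed yoga participants against all controls: 15 of 24 sessions is a moderate threshold, and controls with over 10% missing data are excluded too.
- That the trial's conclusion will rest on it: nothing in the article says so.

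**What to change.** **Wording.** State in the Statistical analysis section that the intention-to-treat result decides the conclusion and that the attendance-based per-protocol result is supportive only. Add that the attendance criterion applies to the yoga arm and the missing-data criterion to both arms. This costs two sentences and removes most of the risk.

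**Estimator.** Replace or supplement the per-protocol analysis with two-stage least squares: randomised arm as instrument, the same baseline covariates, and all randomised participants with the planned multiple imputation. Controls receive no trial yoga, so non-compliance is one-sided and the model is simple. Preferably use the number of sessions attended as the exposure, with attendance of at least 60% as a sensitivity analysis.

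**Downsides.** The interval is wider: in the simulations above the standard deviation of the estimate rose by a factor of about 1.3 (0.22/0.17) to 1.4 (0.26/0.18). The method also assumes that assignment affects the outcome only through the chosen exposure; with session counts, it further assumes that benefit is roughly proportional to sessions. With the 60% threshold that assumption can fail in yoga's favour. If a share p reaches 60% and the others gain δ from partial attendance or home practice, the estimate for those reaching the threshold is too large by δ·(1 − p)/p, which is 0.43δ at p = 0.7 and 0.67δ at p = 0.6. This is why the session count is the better main exposure. No change to trial conduct or data collection is needed, because class attendance is already recorded.
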